## Introduction

The postpartum period, defined by the World Health Organization (WHO) as the period from childbirth to the 42nd day following delivery, is an important period for preventive strategies as common maternal and child health problems become apparent. Health problems include maternal and neonatal infections, postpartum hemorrhage, neonatal respiratory and feeding problems, and psychological problems of varying severity [1]. The purpose of maternity care provided during this period is manifold; 1) to promote physical health of the mother and her baby, 2) to promote coping of parents with the new situation through providing support, and 3) to promote parental empowerment in handling their baby [1, 2]. To achieve this, maternity care consists not only of medical care, but also of psychosocial care, support, and education. Maternity care assistants (MCAs) provide care following delivery at home on a daily basis for over a week (Table 1).

**Table 1 Tab1:** The Dutch perinatal care system

Dutch perinatal care system	

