### Outcomes

#### Primary outcome

The primary outcome is the prevalence of a low maternal empowerment score postpartum, defined as a score beneath the 20th centile of all empowerment scores within the control arm (Table 3). Maternal empowerment will be assessed via the MEQ at the last day of the provided maternity care, usually at day eight after childbirth, and will be defined as the median score across four out of five domains within the MEQ (i.e. scores from the domain ‘Maternity care’ will not be considered for the primary outcome (Table 3)) [20].

**Table 3 Tab3:** Primary and all secondary outcomes at the individual level with definitions and timing of assessment

Outcomes	Postpartum period	
	Early (1–2 weeks after childbirth)	Late (6–12 weeks after childbirth)
Primary	*Maternal empowerment*	
Definition	Low empowerment score (no/yes) defined as a score beneath the 20th centile within the control group	
Assessment	Maternal Empowerment Questionnaire (MEQ). Overall scoring based on the median score across the following four domains; “Looking after yourself”, “My baby”, “My family”, “The future”. Values per question: 1 “Never” 2 “Sometimes”, 3 “Usually”, and 4 “Always”.	
Secondary	*Maternal health related quality of life*	*Maternal depression (postnatal depression)*
Definition	Continuous outcome ranging from zero (dead) to one (full health).	Dichotomous outcome based on the sum score: “No” sum score < 13 and “Yes” sum score > 12.
Assessment	5-level EQ-5D (EQ-5D-5 L). Each dimension within the questionnaire has 5 levels: 1 “no problems”, 2 “slight problems”, 3 “moderate problems”, 4 “severe problems”, and 5 “extreme problems”. Resulting in health profiles ranging from “11,111” through “55,555”. Continuous score calculated with the obtained profiles of the questionnaire with the validated EQ-5D-5 L calculator.	Edinburgh Postnatal Depression Scale (EPDS). Ten item scale. Responses are scored 0, 1, 2 and 3 based on the seriousness of the symptom. Range 0–30.
	*Maternal perceived health*	*Maternal health care utilization*
Definition	Continuous outcome ranging from zero (the worst health possible) to 100 (the best health possible).	Categorical outcome: “No additional care”, “One visit to the A and E department, GP, or GP out-of-hours service”, “Multiple visits”, and “Admission in a hospital”

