Assessment	EuroQol-visual analogue scales (EQ-VAS) represented by a 20 cm vertical scale.	Q1: Since your baby was born, have you had any symptoms for which you have been to the accident and emergency (A and E) department, GP or out-of-hours GP service?
		Q2: Have you been admitted to hospital since your baby was born?
		*Neonatal health care utilization*
Definition		Categorical outcome ranging from: “No additional care”, “One visit to the A and E department, GP, or GP out-of-hours service”, “Multiple visits”, and “Admission in a hospital”
Assessment		Q1: Have you been to the accident and emergency (A and E) department, GP or out-of-hours GP service for your baby since he or she was born?
		Q2: Has your baby been admitted to hospital since he or she was born?
	*Maternal cigarette use*	*Maternal cigarette use*
Definition	Dichotomous outcome (no/yes): “Yes” defined as any usage	Dichotomous outcome (no/yes): “Yes” defined as any usage
Assessment	Q: Do you smoke?	Q: Do you smoke?
	*Maternal alcohol use*	*Maternal alcohol use*
Definition	Dichotomous outcome (no/yes): “Yes” defined as any usage	Dichotomous outcome (no/yes): “Yes” defined as any usage
Assessment	Q: Do you drink alcohol?	Q: Do you drink alcohol?
	*Maternal drugs use*	*Maternal drugs use*
Definition	Dichotomous outcome (no/yes): “Yes” defined as any usage	Dichotomous outcome (no/yes): “Yes” defined as any usage
Assessment	Q: Do you use drugs? Marijuana, hash and weed are drugs too.	Q: Do you use drugs? Marijuana, hash and weed are drugs too.

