### Statistical methods

All analyses will be performed according to the intention-to-treat principle.

Descriptive statistics will be presented, and formal inference will be based on hypothesis testing with two-sided statistical significance assessed at the 5% level.

Multiple imputation using chained equations will be used to account for missing data in baseline characteristics. We will analyze the effect of the intervention on our primary and secondary outcome measurements using multilevel mixed-effects linear or logistic regression analyses with an assumed random effect for each cluster.

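### Health care utilization is counted from birth until the woman answers, so observation time can differ up to twofold (6 to 12 weeks) between women

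*Protocol article*

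**What the plan says.** Table 3 of the protocol article lists maternal and neonatal health care utilization as late postpartum secondary outcomes. The maternal scale is given as "Categorical outcome: “No additional care”, “One visit to the A and E department, GP, or GP out-of-hours service”, “Multiple visits", with hospital admission as the fourth level. The neonatal scale has the same four levels.

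Four questions feed these scales, and all four run from the birth without an end date. For the mother they are the visit question, "Since your baby was born, have you had any symptoms for which you have been to the accident and emergency (A and E) department" (it goes on to name the GP and the out-of-hours GP service), and "Have you been admitted to hospital since your baby was born". The two questions about the baby use the same open recall.

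On timing, the Table 3 column is headed "Late (6–12 weeks after childbirth". The Participant timeline section says the third questionnaire is electronic and is sent six weeks after the birth. It gives no closing date.

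On analysis, the Statistical methods section says "We will analyze the effect of the intervention on our primary and secondary outcome measurements" by "multilevel mixed-effects linear or logistic regression analyses with an assumed random effect for each cluster". It mentions no adjustment for time since birth.

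**The concern.** A count of events since birth depends on how long each woman has been observed. One woman answers in the week the questionnaire arrives and another near the end of the Table 3 window. They may have the same underlying use of care, yet the second has had up to twice as long to move from no contact to one visit, or from one visit to several. The outcome then mixes use of care with delay in answering.

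If delay is similar in the two arms, the result is extra noise and blurred categories. If one arm answers later on average, that arm appears to use more care when it does not. With only ten clusters, differences in response timing between organizations might not balance out across arms, though nothing in the article shows that such differences exist.

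**Working it through.** The plan states no figure for the utilization outcomes, so there is none to reproduce. The check has two steps.

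**1. Setting the texts side by side.**

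- Start of observation: birth, for all four items (Table 3).
- End of observation: the day the woman answers, since no item has a cut-off.
- Earliest answer: about week 6 (Participant timeline).
- Latest answer: week 12 (Table 3 column heading).

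The ratio between the ends is 12/6 = 2. The two timing statements are compatible if six weeks is the sending date and 6–12 weeks is the response window. On that reading, following the plan exactly gives unequal observation time.

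**2. Size.** The article gives no contact rates, so these are assumptions: a constant contact rate, and a proportion p6 of 20%, 30% or 40% with any contact by week 6. The proportion with any contact by week t is then

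p(t) = 1 − (1 − p6)^(t/6).

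| p6 | p(7) | gain from one week's delay | p(12) = 1 − (1 − p6)² | odds ratio, week 12 vs week 6 |
|---|---|---|---|---|
| 20% | 22.9% | 2.9 points | 36% | 2.25 |
| 30% | 34.0% | 4.0 points | 51% | 2.43 |
| 40% | 44.9% | 4.9 points | 64% | 2.67 |

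The odds ratio simplifies to (2 − p6)/(1 − p6); for example, 1.8/0.8 = 2.25.

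The split between one visit and several also moves. If visits follow a Poisson process with mean μ = −ln(1 − p(t)), the chance of two or more is 1 − (1 − p(t))(1 + μ). From week 6 to week 12 it rises from 2.1% to 7.4%, from 5.0% to 16.0%, and from 9.4% to 27.2% for the three values of p6.

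To illustrate bias, suppose women answer at 6.5 weeks in one arm and at 8 weeks in the other (an assumption; the article suggests no such gap). With no treatment effect, any contact would be 21.5% vs 25.7%, 32.0% vs 37.8%, or 42.5% vs 49.4%. The spurious odds ratios are about 1.27, 1.29 and 1.32.

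**The case against.** The strongest reply is that every woman is sent the questionnaire at the same time, six weeks after birth. The spread then comes only from delay in answering, and most women may answer soon after it arrives. No text suggests that the arms are contacted at different times, and the article does not say that completion dates go unrecorded. This stands. It makes the week-12 column above an extreme, and the one-week figure the better guide to typical size. A contact rate that falls after the first weeks would shrink the effect further. What remains is that Table 3 admits answers up to week 12 and nothing in the items or the model allows for it.

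Three stronger readings are tempting, and the documents do not support them.

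- A reader might infer that the stated models cannot handle four categories, or that a binary split would be picked from the data. Ordinal and multinomial models are forms of logistic regression, and nothing says these outcomes will be dichotomised. The sentence covers all outcomes at once, and naming a model for each is commonly left to the analysis plan.
- A reader might infer that the number of visits is not collected, because the questions ask whether a visit took place. Table 3 prints only the question stems for these items. The four categories may themselves be the response options.
- A reader might infer that the protocol breaks its own definition of postpartum, "the period from childbirth to the 42nd day following delivery". That is the WHO definition, given as background in the Introduction. Table 3 sets its own late period, so assessing after day 42 is no contradiction.

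**Conclusion.** The concern holds in a limited form. The utilization items have an open recall period, and the plan allows answers from week 6 to week 12, so observation time is unequal by up to a factor of two at the extremes. The effect is noise in two secondary outcomes. It becomes bias only if response timing differs by arm, which the article neither shows nor rules out.

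Under a constant rate with 20–40% in contact by week 6, each week of delay near week 6 adds about 3–5 percentage points. These sizes are illustrations. The fact of unequal windows rests on the text alone. The primary outcome and the sample size are not touched, so this is a minor improvement. The missing name of an ordinal model is a matter of wording and not an error.

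**What to change.** Preferred: word all four items to cover a fixed window that every woman has completed when she answers, namely the first six weeks after birth. This costs a small edit to an electronic form. Its downside is that late responders must recall an earlier period with a set end.

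If the form is already in use: take the completion date, calculate weeks since birth, and include it as a covariate in the models for the two utilization outcomes. Preferably add a sensitivity analysis limited to women who answered soon after six weeks, with the limit set in advance. The downside is that completion time arises after randomisation. If the intervention affects when women answer, both the adjustment and the restriction can themselves distort the comparison, so response timing should be reported by arm.

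In either case, state in Table 3 or the Participant timeline section that six weeks is the sending date and when responses close.

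As a clarification, add one line to Statistical methods: the four-level utilization outcomes are analysed by mixed-effects ordinal logistic regression, with the proportional-odds assumption checked. The check matters because an admission is a different kind of event from a visit and can occur without one.

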### Data monitoring

A data monitoring committee (DMC) is not installed, as the ethics committee deemed it as unnecessary, because the risks for participants are negligible. All aspects of the intervention fall within the scope of conventional maternity care.

The funding source has no role in the design of the study, and neither in the collection and management of the data.

## Discussion

With this C-RCT we aim to systematically increase the identification of non-medical risk factors during pregnancy, and use the obtained risk profile for improved client-tailored care during the postpartum period. We envisage that this intervention creates an additional opportunity for MCAs to empower women during the postpartum period. Increased maternal empowerment has the potential to enhance their self-efficacy, their quality of life, and their child’s well-being during the postpartum period [10, 13].

To our knowledge this is the first multicenter trial of client-tailored, risk-guided maternity care, creating a unique opportunity to investigate its potential to improve maternal empowerment. In concordance with the overall aim of the HP4All-2 program, this study targets women from deprived neighborhoods, aiming to reduce adverse maternal and neonatal outcomes of those who are at greatest risk.

There are several challenges in the execution of this complex C-RCT that merit discussion. This C-RCT is embedded in a complex existing collaborative setting involving multiple municipalities and maternity care organizations and their professionals. Particular challenges include maintaining engagement in 17 sites spread across the country, engaging staff groups employed by different organizations, and motivating MCAs from different organizations to change their routine working practices and adapt to a more risk-guided provision of care. In addition, there is an unequivocal registration of the personalized care undertaken by maternity care professionals during the postpartum.

To conclude, this C-RCT is the first trial in the Netherlands aiming to empower women during the postpartum period. Providing a risk assessment, with emphasis on non-medical risks related to SES and psychopathology, facilitates client-tailored care and may contribute to prevention of adverse health outcomes for mother and child.

## Abbreviations

C-RCT: Cluster Randomized Controlled Trial
HP4All-2: Healthy Pregnancy 4 All-2
ICC: Intraclass Correlation Coefficient
MCA: Maternity Care Assistants
MEQ: Maternal Empowerment Questionnaire
SES: Socioeconomic status
VIF: Variance Inflation Factor
